### Constraint induced movement therapy (CIMT)

2.5

Each subject will receive 14 days (2-week period: 10 weekdays) of CIMT (using the same methodology as described in a recent multi-site clinical trial.^[15]^ furthermore, during the 10 weekdays of the treatment period, the individuals participating will come into the laboratory to train the affected arm for up to 6 hours a day, using a variety of tasks according to a behavioral technique termed “shaping.”

**Statistical power and data analysis Sample size** will be determined with reference to other studies that used similar endpoints. We assume that a standardized difference of 0.8 (the difference between groups divided by the standard deviation) is conservative to detect a clinically meaningful difference between groups (active 1 Hz rTMS prime with tDCS/CIMT and sham tDCS/CIMT). We will assume a type I error of 5% (alpha), a type 2 error of 10% (beta), therefore, the power is going to be 90%. A t-test will be used (Using the sample size calculation for a normal distributed population); where 15 individuals per arm will be needed (therefore, a total of 30). We expect a 20% rate of loss to follow up or drop out. Moreover, we will assume that individuals who drop out will not improve from the last measured point; therefore, the sample size will increase by 20% to 36 participants (18 per arm). Furthermore, in case of unexpected factors such as higher placebo response, we increased the sample size further to 40 patients.

**PROTECTION OF HUMAN SUBJECTS** This study aims to enroll adult patients with a history of cerebral infarct that is chronic and associated with stable and significant motor deficits. Both ischemic and hemorrhagic stroke subtypes will be included. The entry criteria for patient enrollment are the following:

(1)age 18 to 90;(2)first-time clinical ischemic or hemorrhagic cerebrovascular accident as noted in the radiological (or physician's) report;(3)the ability to extend =20° at the wrist and 10° at the metacarpophalangeal and interphalangeal joints of all digits;(4)participants must demonstrate adequate balance while wearing the restraint;(5)the ability to stand from a sitting position and the ability to stand for at least 2 minutes with or without upper extremity support;(6)weakness, defined as score of 15 to 55 (out of 66) on arm motor Fugl-Meyer scale; and(7)stroke onset more then 6 months prior to study enrollment.

*Exclusion criteria*:

(1)having significant disability before stroke;(2)any history of depression before the stroke (where appropriate);(3)Any considerable decline in language reception, alertness or attention that might hinder with understanding the instructions for the motor testing;(4)excessive pain in any joint of the paretic extremity;(5)contraindications to single-pulse TMS (TMS will be used to measure cortical excitability) such as metal head implants;(6)advanced cardiac, pulmonary, kidney or liver disease;(7)a terminal medical diagnosis consistent with survival 1 year;(8)coexistent major neurological or psychiatric disease (to decrease the number of confounders);(9)a history of significant drug abuse in the prior 6 months;(10)the use of certain neuropsychotropic drugs such as tricyclics, antidepressants, or 51 of 66 carbamazepine;(11)active enrollment in a separate intervention study targeting stroke recovery;(12)previously applied constraint-induced motor therapy and/or tDCS treatment for stroke; and(13)a history of epilepsy before stroke (or episodes of seizures within the last six months).

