### Overall strategy

2.1

Overall Approach, Participants, and Feasibility: We propose to study 40 patients (above 18 years) with first-time clinical ischemic or hemorrhagic cerebrovascular accident. Individuals with preexisting neurological or psychiatric conditions, those with unstable medical conditions, and those on any medication that might alter the TMS-tDCS measures will be excluded. A written consent will be obtained, and all the subjects will have full neurological and medical examination. Furthermore, detailed neuropsychological and behavioral assessment will also be performed in different domains. All participants will undergo a neurophysiologic study of local cortical reactivity, plasticity, and network dynamics using TMS-EMG following stroke. Participants will be randomized to active treatment with 1 Hz rTMS prime with real anodal or sham tDCS by means of randomization stratification. This approach guarantee that both groups have a close distribution in regards to the degree of paresis. Participants will be gathered into groups (strata) defined by the degree of paresis (low and high functional) and then randomized separately within each stratum according to a block randomization of 4 to receive real 1 Hz rTMS prime tDCS/CIMT and sham tDCS/CIMT. All participants will undergo brain magnetic resonance imaging (MRIs) for morphometric analysis and diffusion tensor imaging, and serial neurological and neuropsychological exams.

We have developed a safe and reliable method combining TMS with EMG to characterize cortical reactivity, plasticity, and brain network dynamics in humans.^[23–27]^

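### The only between-group test named is a t-test with no mention of baseline hand function or the paresis stratum; an adjusted model should be prespecified, though its gain depends on a correlation the article does not give

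*Protocol article*

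**What the plan says.** Section 2.5 of the protocol article has a paragraph on statistical power and data analysis. It states: "We assume that a standardized difference of 0.8 (the difference between groups divided by the standard deviation"; "We will assume a type I error of 5% (alpha"; "a type 2 error of 10% (beta), therefore, the power is going to be 90" per cent; then "A t-test will be used (Using the sample size calculation for a normal distributed population"; and "where 15 individuals per arm will be needed (therefore, a total of 30". The total is raised to 36 for dropout ("We expect a 20% rate of loss to follow up or drop out") and then to 40. No other between-group efficacy test and no covariate is named anywhere in the article.

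Section 2.1 defines two paresis strata, low and high functional, and patients are "randomized separately within each stratum according to a block randomization of 4". Section 2.3 names the Jebsen Taylor test and the Purdue Pegboard as the efficacy instruments, describes efficacy as change in motor function, and schedules the instruments in the week before treatment as well as afterwards. The article does not say whether the t-test compares final or change scores, which standard deviation scales the 0.8, whether the test is one- or two-sided, or how strongly baseline predicts outcome.

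**The concern.** The design stratifies on paresis, presumably because paresis is expected to predict hand function, and it measures each efficacy score before treatment. The one test named uses neither as a covariate.

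Stratified randomization removes between-arm variation due to the stratum from the treatment comparison. An unadjusted t-test still counts that variation in its standard error. The test is therefore conservative whenever the stratifier is prognostic. Baseline variation within strata also stays in the error term if final scores are compared. With 40 patients and power well below the stated figure, the wasted precision matters.

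**Working it through.** **Inputs from the article (section 2.5):** d = 0.8, alpha 5%, power 90%, two-group t-test, 15 per arm, planned total 40 (20 per arm), 20% loss. **Assumptions:** two-sided test; r, the correlation of outcome with baseline and stratum, is not given, so a range is shown.

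**1. The plan's own figure.** n per arm = 2(z₀.₉₇₅ + z₀.₉₀)²/d² = 2(1.960 + 1.282)²/0.64 = 32.8, so 33, or 34 with the t distribution. One-sided: 2(1.645 + 1.282)²/0.64 = 26.8, so 27, or 28 with t. The stated 15 is not reproduced either way.

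**2. Power of the unadjusted t-test.** Noncentral t with 2n − 2 degrees of freedom and noncentrality 0.8·√(n/2): 56% at 15 per arm, 59% at 16, 65% at 18 and 69% at 20. At 20 per arm, 90 − 69 = 21 points are missing. One-sided power at 20 per arm is 80%.

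**3. Adjusted model, 0.8 in final-score SD units.** The residual SD is √(1 − r²), so the effective difference is 0.8/√(1 − r²), with 2n − 4 degrees of freedom. For r = 0.5 it is 0.8/√0.75 = 0.924. The 16-per-arm row is 20 × 0.8, where lost patients contribute nothing.

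| r | 0 | 0.3 | 0.5 | 0.6 | 0.7 | 0.8 |
|---|---|---|---|---|---|---|
| 20 per arm | 69% | 73% | 81% | 87% | 93% | 98% |
| 16 per arm | 59% | 63% | 71% | 78% | 86% | 95% |

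At 20 per arm the gain is 73 − 69 = 4 points at r = 0.3 and 81 − 69 = 12 points at r = 0.5. The full 90% is reached from r of about 0.65.

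**4. Adjusted model, 0.8 in change-score SD units.** With equal SDs before and after, the change-score SD is √(2(1 − r)) final-score SDs. The effective difference is 0.8·√(2(1 − r))/√(1 − r²) = 0.8·√(2/(1 + r)).

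| r | 0.3 | 0.5 | 0.7 | 0.9 |
|---|---|---|---|---|
| 20 per arm | 86% | 81% | 76% | 71% |

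The comparator is a t-test on change scores, again 69%. Here the gain shrinks as r rises, and 90% is not reached in this range.

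**5. Conservatism of the t-test.** Simulation of 40 patients, two strata, blocks of 4 and no treatment effect. When the stratum is close to a split of the baseline score, the t-test on final scores rejects in roughly 3% to 4% of trials at r = 0.5 and about 2% at r = 0.7, against a nominal 5%. The adjusted model stays at about 5%. When the stratum tracks baseline more loosely (underlying correlation 0.6), the t-test rejects in about 4.4% and 3.7%. The shortfall below 5% depends on how closely stratum and baseline agree, which the article does not say.

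**6. Cost when baseline predicts nothing.** Simulated power at 20 per arm and r = 0 is 68% adjusted against 70% unadjusted. The loss of about 2 points comes from two degrees of freedom and chance covariate imbalance.

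**The case against.** The quoted sentence sits in sample-size reasoning, in an article that condenses a fuller protocol. A t-test formula is often paired with an adjusted analysis, covariates are commonly left to the SAP, and nothing in the article excludes adjustment. This stands: the article does not mention adjustment, which is less than ruling it out. What remains is that the t-test is the only test named, under a lead-in that covers data analysis, and it does not match the stratified design.

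A reader might infer three stronger claims that the article does not support.

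- *The plan ignores baseline.* Efficacy is described as change in motor function, and a t-test on change scores already uses baseline.
- *Adjustment restores the missing power at no cost.* This needs a correlation that the article does not give. The gain is small at 0.3 and absent at 0, and under change-score scaling it stays short of 90% in the range shown. The wide Fugl-Meyer entry range (15 to 55) does not settle it: that scale characterizes baseline, and the efficacy instruments are others.
- *The t-test is biased or risks false positives.* Stratification already balances paresis, and the unadjusted test errs on the cautious side.

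**Conclusion.** The concern holds as a matter of efficiency and of matching the analysis to the design. At 20 per arm, adjustment raises power from about 69% to between 73% and 98% for r from 0.3 to 0.8 on the final-score scale. On the change-score scale it raises power to between 71% and 86% for r from 0.9 down to 0.3. In both cases adjustment beats the t-test unless r is near zero, where it may lose about 2 points. These figures assume d = 0.8, a two-sided 5% test, normal outcomes and a linear relation to baseline.

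Adjustment does not repair the sample size. The article's own inputs require about 34 per arm, not 15, and even with adjustment at r = 0.5 on the final-score scale, 26 per arm are needed for 90% before dropout.

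**What to change.** Before unblinding, prespecify as the primary analysis a linear model of the post-treatment score on arm, the baseline value of the same score and paresis stratum, or the same terms in a repeated-measures model. Report the adjusted difference with its 95% confidence interval, and keep the t-test as a sensitivity analysis, stating whether it uses final or change scores. If the SAP already specifies such a model, the article's t-test and sample-size text should be reconciled with it.

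State sidedness, which SD scales the 0.8 and the assumed correlation with its source. Then redo the sample size, or restate the power that 40 patients provide.

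The model change costs wording and two degrees of freedom, with no extra patients or visits. Correcting the sample size is a separate matter and may require more patients or a lower stated power.

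### Fifteen patients per arm do not give 90% power for a standardized difference of 0.8: a two-arm t-test needs 34 per arm (28 if one-sided), and the planned 40 patients fall short too

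*Protocol article*

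**What the plan says.** The sample size paragraph stands at the end of section 2.5 of the protocol article, under the heading on constraint-induced movement therapy. It gives nearly everything needed to check it:

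- Effect size: "We assume that a standardized difference of 0.8 (the difference between groups divided by the standard deviation) is conservative".
- Comparison: a "clinically meaningful difference between groups (active 1 Hz rTMS prime with tDCS/CIMT and sham tDCS/CIMT", that is, two separately randomized arms, as section 2.1 also describes.
- Error rates: "We will assume a type I error of 5% (alpha", and "a type 2 error of 10% (beta), therefore, the power is going to be 90" percent.
- Test: "A t-test will be used (Using the sample size calculation for a normal distributed population".
- Result: "where 15 individuals per arm will be needed (therefore, a total of 30".

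The total of 30 is then raised by 20% to 36 (18 per arm) for loss to follow-up, with dropouts assumed not to improve beyond their last measurement. It is raised again to 40 for unforeseen factors such as a larger placebo response. The paragraph does not state whether the test is one- or two-sided, and it mentions no baseline adjustment, correlation or repeated-measures gain.

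**The concern.** Detecting 0.8 SD between two independent groups with 90% power is a familiar calculation, and its answer is in the low thirties per arm. Fifteen is less than half of that. Inputs and result are printed together, so this is a statement that can be checked, and a fuller protocol or an analysis plan could not make it true.

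The 90% power is the property by which a reader will judge a negative result. If the real power is far lower, failure to find a difference would be read as evidence against an effect of 0.8 SD when the trial had a substantial chance of missing one. The totals of 30, 36 and 40 all build on the figure of 15, so the error runs through the whole justification.

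**Working it through.** **Inputs, all from the sample size paragraph.** d = 0.8; alpha = 0.05; power = 0.90; two independent arms, 1:1; unadjusted t-test. Sidedness is not given, so both readings are shown.

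**Required number per arm.** The normal approximation is n = 2(z_alpha + z_beta)² / d².

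- Two-sided: 2 × (1.960 + 1.282)² / 0.64 = 32.8, so 33 per arm. The exact noncentral t gives 33.8, so **34 per arm** (68 in total).
- One-sided: 2 × (1.645 + 1.282)² / 0.64 = 26.8, so 27 per arm. The exact noncentral t gives 27.5, so **28 per arm** (56 in total).

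**Attempts to reproduce 15 per arm.**

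| Variant | Result |
|---|---|
| Two-sample t, 90% power, two-sided / one-sided | 33.8 / 27.5 |
| Two-sample t, 80% power, two-sided / one-sided | 25.5 / 20.03 |
| Normal formula without the factor 2 for two arms, two-sided / one-sided | 16.4 / 13.4 |
| One-sample or paired t, 90% power, two-sided / one-sided | 18.4 / **14.8** |

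Only the one-sided one-sample or paired test rounds up to 15, and that test does not compare two arms. The match suggests where the number may have come from, but the article does not say.

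**Power at d = 0.8 (exact noncentral t), and the difference detectable with 90% power two-sided.**

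| Per arm | Origin | Power, two-sided | Power, one-sided | Detectable, two-sided |
|---|---|---|---|---|
| 15 | stated requirement | 56.2% | 68.9% | 1.23 SD |
| 16 | 40 enrolled, 20% lost: 20 × 0.8 | 59.1% | 71.4% | 1.18 SD |
| 18 | 36 enrolled, no loss | 64.5% | 76.0% | 1.11 SD |
| 20 | 40 enrolled, no loss | 69.3% | 79.9% | 1.05 SD |

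**Dropouts kept in the analysis.** The article assumes dropouts do not improve after their last measurement. If they are retained on that basis, n stays at 20 per arm but the effect is diluted. As an extreme assumption, let 20% of each arm contribute no effect and leave the SD unchanged. Then d = 0.8 × 0.8 = 0.64, and two-sided power at 20 per arm is about 51%.

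**What 90% power would need.** Two-sided with 20% loss: 34 / 0.8 = 42.5, so 43 per arm, 86 in total.

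**Could baseline adjustment rescue it?** Adjusting for a baseline value with correlation r shrinks the residual SD by √(1 − r²), so reaching 90% requires 0.8/√(1 − r²) to equal the detectable difference above. At 20 per arm, r = √(1 − (0.8/1.052)²) ≈ 0.65. At 16 per arm, r = √(1 − (0.8/1.185)²) ≈ 0.74. The article names a t-test and gives no correlation.

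**The case against.** The strongest reply accepts that 15 does not follow, but holds that 34 per arm and 56% power overstate the problem. Sidedness is not stated, the hypothesis in the abstract is directional, and the trial enrols 40 patients, not 30. On the most favourable reading (one-sided, all 40 complete) power is 80%. That is fair as to size, and the two-sided figures should be labelled as an assumption. It does not remove the error: even this reading misses 90%, and no two-arm reading yields 15.

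A second point is that quoting 16 evaluable per arm treats dropouts as removed, whereas the article seems to keep them with a carried-forward value. This also stands, so the 16-per-arm figures describe one possible handling and not the plan's own rule. Carrying dropouts forward without improvement dilutes the effect, however, so it offers no rescue.

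Third, whether 0.8 SD is a conservative effect size is separate from whether the sample size suits it, and it depends on studies not shown here. That is correct. The arithmetic does not show that 0.8 is too large. It shows only that the word cannot be taken to mean that the design has a margin.

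Finally, the one-sample or paired origin of 15 is conjecture, and nothing in the conclusion depends on it.

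**Conclusion.** The concern holds. From the article's own inputs the requirement is 34 per arm two-sided or 28 one-sided, against a stated 15. The statement that "therefore, the power is going to be 90" percent is therefore wrong for 30 patients, and it remains wrong for the 40 to be enrolled. At 15 per arm, power is 56% (two-sided) or 69% (one-sided). At 20 per arm with no losses it is 69% or 80%. On the two-sided reading, the chance of missing a true 0.8 SD effect is 31% with all 40 analysed and 41% with 16 per arm, against the 10% stated.

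These figures assume an unadjusted two-sample t-test with equal arms and normally distributed outcomes. The choice of sidedness changes their size but not the conclusion. This must be corrected, because a central stated property of the design is not one that the design has.

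**What to change.** Rewrite the sample size paragraph. The least costly version keeps 40 patients and says what they provide: with 20 per arm and an unadjusted two-sided 5% t-test, about 69% power for 0.8 SD, or 90% power for about 1.05 SD. Add a figure that allows for 20% loss and matches the way dropouts will be analysed. If they are excluded, leaving 16 per arm, that is about 59% power for 0.8 SD, or 90% power for about 1.18 SD. If they are carried forward, state the assumed dilution and recompute. State the sidedness. Remove 15 per arm and 90% power, and drop the description of 0.8 as conservative unless the supporting data are given.

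This costs a rewording and a less favourable stated power, with no extra patients.

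If 90% power for 0.8 SD is to be kept, there are two routes. One is to enrol about 86 patients (two-sided, 20% loss). The other is to make a baseline-adjusted analysis primary and justify a baseline correlation of about 0.65 (20 per arm analysed) to 0.74 (16 per arm analysed).

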These instruments will be performed at the following time points by trained staff blinded to group assignment: during the week before the beginning of treatment (2) During day 5 and day 10 of treatment and (3) at 2 weeks of follow up, 4 weeks and 6 months after the end of treatment (Table 1). Moreover, to make sure that blinding is not broken within the duration of the study, we will use a questionnaire to assess the validation of the blinding at the end of the study. This questionnaire will ask both the participants and the rater whether the treatment was sham or active tDCS. The confidence of the responses will be rated accordingly, from 0 to 5, where 5 is total confidence and 0 is no confidence,

**Table 1 T1:** Stroke and plasticity schedule of events.

	Screening visit	Training and tDCS Visits (10 d)			Follow-up visit
	1	2	6	10	4 wk
Consent	X				
Inclusion/Exclusion	X				
Pregnancy Test if indicated	X				
PMH/Physical	X				
Demographics	X				
Taylor Hand Function Test	X				X
Purdue Pegboard Test	X				X
Fugl-Meyer Assessment of Motor Recovery	X				X
Modified Barthel Index	X				X
Modified Ashworth Scale	X				X
Visual analog scale	X				X
Mini Mental State Examination		X	X	X	X
TMS and tDCS Screen	X	X	X	X	X
Training		X	X	X	X
MRI	X		X		
Pre/Post TMS Side Effect Questionnaire		X	X	X	X

MRI = magnetic resonance imaging, tDCS = transcranial direct current stimulation, TMS = transcranial magnetic stimulation.

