### TMS methodology

2.4

Navigated Brain Stimulation (NBS) system (ANT, NLtm) will be used to deliver TMS by a figure-of-eight (F8) coil coupled with a Magpro stimulator (MagVenture, Denmark). Navigated TMS has the ability to online monitor the targeted cortical region, coil position, and orientation within and across sessions by using structural MRI. It delivers trial-by-trial information of an induced electric field for each TMS pulse and the localization of the induced current maxima. Data obtained by this system are reproducible, which is an essential aspect of this type of study. The display of induced currents and calculation will assist to overcome the constraints of TMS by targeting relevant structures of brain alone. As differences between different individuals in structure–function relationships, may change the induced currents and precision of the neuronavigation system, particularly in individuals with brain pathology.^[28]^

**The repetitive TMS paradigm** will be administered at 1 Hz frequency and consist of 2000 pulses delivered over a 30 minute period at 90% of the patient's motor threshold. These parameters are known to cause brain activity inhibition. The optimal stimulation site (First dorsal interosseus and APB muscles), active and resting threshold will be established in the unaffected and affected hemispheres. Assessment of EMG signals will be done at a rate of 5000 Hz. Cortical silent period (cSP) and resting and active motor threshold (RMT, AMT) will be analyzed according to the IFCN guidelines.

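### Exclusion 5 treats TMS as a single-pulse measuring tool and exclusion 12 does not bar prior rTMS, although 1 Hz rTMS is part of the treatment

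*Protocol article*

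**What the plan says.** The Protocol article prints a numbered list of 13 exclusion criteria at the end of section 2.5. Two of them concern brain stimulation directly:

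- Exclusion 5: "contraindications to single-pulse TMS (TMS will be used to measure cortical excitability) such as metal head implants".
- Exclusion 12: "previously applied constraint-induced motor therapy and/or tDCS treatment for stroke".

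Elsewhere the article makes repetitive TMS part of the treatment:

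- Section 2.1 (Overall strategy): "Participants will be randomized to active treatment with 1 Hz rTMS prime with real anodal or sham tDCS".
- Section 2.4 (TMS methodology), on the repetitive paradigm: it "will be administered at 1 Hz frequency and consist of 2000 pulses delivered over a 30 minute period", at 90% of the motor threshold.
- Section 2.5, in the sample-size paragraph, the comparison is between "active 1 Hz rTMS prime with tDCS/CIMT and sham tDCS/CIMT".

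The hypothesis in the Abstract also includes low-frequency rTMS on the healthy side. Section 2.4 further describes anodal tDCS at 1.5 mA for 20 minutes, and an assessment of cortical excitability by single- and paired-pulse TMS.

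**The concern.** Eligibility criteria for a stimulation trial should cover what is actually delivered. Exclusion 5 asks only about single-pulse TMS, and its bracketed explanation gives TMS a measuring role. That suits a trial of tDCS with CIMT in which TMS is an assessment. In this trial patients also receive repetitive TMS as treatment.

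Exclusion 12 shows the same mismatch. It keeps out patients who have already had CIMT or tDCS for stroke, but it admits those who have already had rTMS for stroke, and no reason is given for the difference.

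Two things are at stake. One is whether the written safety criterion asks about the stimulation that patients will receive. The other is whether the rule on prior treatment is applied consistently across the components under test.

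**Working it through.** No arithmetic beyond a count applies, and the plan gives no figure to reproduce. The check sets the criteria beside the intervention.

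**Step 1: is rTMS a treatment here?** Yes, in four places: the hypothesis (Abstract), the randomised treatment (section 2.1), the dose paragraph (section 2.4) and the sample-size contrast (section 2.5). These places differ on whether the sham-tDCS arm also receives rTMS: section 2.1 can be read that way, while the Abstract and the sample-size paragraph suggest that it does not. On either reading rTMS is a treatment component, so the point does not depend on resolving this.

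**Step 2: exclusion 5 against what is delivered.**

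| Stimulation in section 2.4 | Role | Named in exclusion 5? |
|---|---|---|
| Single-pulse TMS | Measurement | Yes |
| Paired-pulse TMS | Measurement | No |
| Repetitive TMS, 1 Hz, 2000 pulses | Treatment | No |
| Anodal tDCS, 1.5 mA, 20 minutes | Treatment | No |

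Metal head implants are given only as an example. The governing term is single-pulse TMS.

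**Step 3: exclusion 12 against the treatment components.**

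| Component | Prior use for stroke barred by exclusion 12? |
|---|---|
| CIMT | Yes |
| tDCS | Yes |
| rTMS | No |

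Two of three components are named.

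**Step 4: does another criterion close either gap?**

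- Exclusion 8 (coexistent major neurological or psychiatric disease), exclusion 10 (certain neuropsychotropic drugs) and exclusion 13 ("a history of epilepsy before stroke (or episodes of seizures within the last six months") reduce the safety concern. None mentions prior rTMS.
- Exclusion 11 covers only current enrolment in another stroke-recovery intervention study, not past treatment.
- Section 2.1 excludes preexisting neurological or psychiatric conditions, unstable medical conditions, and drugs that could change the TMS-tDCS measures. It does not mention prior rTMS.
- Table 1 (section 2.3) has a row "TMS and tDCS Screen", marked at the screening visit and at every other listed visit. It names both modalities and so bears on safety; its content is not described.

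The safety gap in exclusion 5 is therefore partly covered. The gap in exclusion 12 is not covered by any stated criterion.

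**The case against.** The strongest reply is that little follows in practice. Metal head implants matter for every form of TMS and are already the stated example. Seizures have their own criterion. No specific contraindication to rTMS or tDCS has been shown to slip past the whole set of criteria. The Table 1 screen names both TMS and tDCS, section 2.3 mentions an inclusion and exclusion checklist, and a journal article may leave the content and pass/fail rule of a screening form to the full protocol. Exclusion 5 also does not say that TMS is used for nothing except measurement.

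Most of this stands. It limits the safety consequence and is why the point is minor. The screen's missing pass/fail rule is no finding. But the article prints the exclusion list item by item, and exclusion 5 is not silent: it states a stimulation type and a purpose that do not fit the treatment described in sections 2.1, 2.4 and 2.5. The reply does not reach exclusion 12 at all.

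A reader might also infer a seizure gap. Inclusion 7 requires "stroke onset more then 6 months prior to study enrollment", while exclusion 13 looks back only six months for seizures, so a seizure after the stroke but more than six months before entry does not trigger that criterion. The documents do not support calling this an error. Exclusion 13 sets an explicit look-back, exclusion 9 uses the same six months for drug abuse, and nothing in the article says that any post-stroke seizure should exclude. Whether a longer period is needed for 1 Hz rTMS is a clinical safety question that these documents cannot settle. The share of post-stroke time left uncovered would measure calendar time under assumed stroke dates, not risk.

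**Conclusion.** The point holds as a minor mismatch between eligibility wording and intervention. Exclusion 5 names one of the two TMS measuring techniques and neither stimulation treatment. Exclusion 12 names two of the three treatment components, so a patient previously treated with rTMS for stroke is eligible while one previously treated with CIMT or tDCS is not.

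The conclusion rests only on the printed criteria and the description of the treatment. The documents do not say how many candidates have had rTMS, so the number of patients affected is unknown. It would go too far to infer that the comparison is biased or loses power, or that patients are shown to be unsafe: assignment is randomised within paresis strata, and several other criteria and the Table 1 screen bear on safety.

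**What to change.** - Reword exclusion 5 to: *contraindications to single-pulse, paired-pulse or repetitive TMS, or to tDCS, such as metal head implants*. Replace the bracketed explanation with a statement that TMS is both a measure and an intervention in this trial.
- Add rTMS to the prior stroke treatments listed in exclusion 12.

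The cost is the wording of two criteria and possibly a few more screen failures. Visits, dose, endpoints and the planned 40 patients stay as they are.
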